This is an open-label study to investigate the mechanism of action of efalizumab (anti-CD11a). After a wash-out period from standard therapies, patients with moderate to severe psoriasis will be treated with subcutaneous injection of 1.0 mg/kg/week efalizumab for 24 weeks.

- Patients will be assessed by the PASI score and a modified, “linear PASI score”. Patients will also be categorized as “*responders*” and “*non-responders*” according to objective outcome criteria (**Clinical Response Score** and **Type-1 Pathway Score**). The primary goal is to study the cellular and genomic basis for therapeutic improvement or resistance to CD11a blockade.

At baseline, an index plaque will be selected for serial biopsy analysis. This plaque is located on the trunk, buttocks, or thigh (sensitive areas such as the face will not be biopsied). Punch biopsies will be performed from the index plaque at baseline (before treatment) and after 2, 6 and 12 weeks of treatment with efalizumab. The response to treatment at 12 weeks will be graded. Complete responders according to the **Clinical Response Score** will be defined as patients that reverse keratin 16 expression in conjunction with reversed acanthosis and normalized differentiation. The clinical responses will be graded from best to worst using a multivariate analysis technique that creates the “**Clinical Response Score**” based on a combination of epidermal thickness, the qualitative pattern of keratin 16 expression, and quantitative expression of keratin 16 mRNA. The stratification of clinical responses by this technique provides a measure of disease improvement that can be subsequently related to quantitative alterations in expression of other disease-related and inflammation-related genes.

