- History of or ongoing uncontrolled bacterial, viral, fungal, or atypical mycobacterial infection
- History of active tuberculosis (TB) or currently undergoing treatment for TB. PPD testing or chest X-ray is required for high‑risk subjects (see Appendix D). Subjects with a positive PPD (not due to BCG vaccination) or chest X-ray will be excluded
- History of opportunistic infections (e.g., systemic fungal infections, parasites)
- Seropositivity for human immunodeficiency virus (HIV)
- Seropositivity for hepatitis B or C virus
- Hepatic enzymes >3 times the upper limits of normal (ULN)
- Diagnosis of hepatic cirrhosis, regardless of cause or severity
- WBC count <4000L or >14,000/L
- Serum creatinine >2 times the ULN
- Hospital admission for cardiac disease, stroke, or pulmonary disease within the last year
- Presence of malignancy within the past 5 years, including lymphoproliferative disorders. Subjects with a history of fully resolved basal cell or squamous cell skin cancer may be enrolled.
- History of substance abuse within the last 5 years
- Any medical condition that, in the judgment of the investigator, would jeopardize the subject’s safety following exposure to study drug

Note: Certain medications and vaccines may not be used for specified periods of time prior to enrollment or at any time during the treatment period. Please see text on page 21 and 22 regarding excluded therapies.

Study Treatment

Formulation

Efalizumab (Raptiva) is manufactured by Genentech. Efalizumab is supplied in single‑use glass vials containing 125 mg of sterile, pyrogen‑free, lyophilized drug product. When reconstituted with 1.3 mL of Sterile Water for Injection (SWFI), each vial contains efalizumab at a concentration of 100 mg/mL. The solution is clear. Reconstituted efalizumab is composed of efalizumab (125 mg), polysorbate 20, L‑histidine hydrochloride, sucrose, and SWFI, USP at a pH of 6.2.

For further details, see the Investigator Brochure.

Dosage, Administration, and Storage

Each subject will receive 24 weekly doses of 1.0 mg/kg study drug. Study drug will be administered by SC injection.

The following formula will be used to calculate dose volume:

| Dose volume (mL) = | Assigned dose (mg/kg)  body weight (kg) |
| --- | --- |
| 100 (mg/mL) |

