If a subject experiences acute adverse events (defined as fever, headache, chills, nausea, vomiting, or myalgia on the day of or the 2 days following an injection of study drug), acetaminophen or other nonprescription, nonsteroidal analgesics are recommended as the first therapy. If these are ineffective, any approved analgesic may be prescribed at the discretion of the investigator. If a subject experiences nausea or vomiting, the subject may be treated with any approved anti‑emetic, as required.

If a subject experiences relapse of psoriasis after withdrawal from efalizumab, systemic or UV therapy may be used to the investigator’s discretion.

Treatment regimens of ‑blockers, angiotensin-converting enzyme (ACE) inhibitors, antimalarial drugs, quinidine, interferon, or lithium should be held constant, if possible, between Day –28 and Day 84. Addition or changes in these medications do not require discontinuation from the study.

Excluded Therapies

The following concomitant therapies are excluded for specified times prior to enrollment and throughout the treatment period:

- Systemic treatments for psoriasis (e.g., PUVA, cyclosporine, corticosteroids, methotrexate, oral retinoids, MMF, thioguanine, hydroxyurea, sirolimus, azathioprine, 6-MP, etanercept) (excluded from Day –28 of the screening period through Day 84)
- Immunosuppressive medications for any indication (excluded from Day –28 through Day 84)
- Live virus or bacteria vaccines, which include, but are not limited to, measles, mumps, rubella, polio, bacille Calmette‑Guerin (BCG), yellow fever, and TY21a typhoid (excluded from Day –14 through Day 84)
- Concomitant experimental drugs or treatments (excluded from Day –28 or five half-lives, whichever is longer, prior to Day 0 through Day 84)

If a subject receives one of the above medications during the screening period, the subject should not be included. If a subject receives one of these excluded concomitant therapies during the treatment period, the subject should not receive any additional doses of study drug and should be discontinued from the study.

The following additional concomitant therapies should be discontinued for at least 14 days prior to treatment:

- UVB phototherapy, tanning booths, or other nonprescription UV light sources
- Topical treatments for psoriasis (e.g., Potency Group I and II topical corticosteroids, calcipotriene, tazarotene, anthralin).

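### Prohibited therapies are barred for the whole treatment period but dated only to Day 84, leaving contradictory rules for the last 12 of 24 weeks of dosing

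*Protocol*

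**What the plan says.** Excluded Therapies begins: "The following concomitant therapies are excluded for specified times prior to enrollment and throughout the treatment period". The note at the end of the Exclusion Criteria repeats the on-treatment part, barring certain medications and vaccines before enrollment "or at any time during the treatment period". A subject who receives a listed therapy during the treatment period "should not receive any additional doses of study drug and should be discontinued from the study".

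Treatment lasts 24 weeks. The synopsis says that patients "will be treated with subcutaneous injection of 1.0 mg/kg/week efalizumab for 24 weeks", and Dosage, Administration, and Storage says "Each subject will receive 24 weekly doses of 1.0 mg/kg study drug". Patients inject themselves in weeks 13-24. Assessments during Treatment includes visits on Days 112, 140 and 168.

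The four items under the lead-in are nevertheless all dated to Day 84:

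- systemic psoriasis treatments: Day –28 to Day 84;
- immunosuppressants: "Immunosuppressive medications for any indication (excluded from Day –28 through Day 84";
- live vaccines: Day –14 to Day 84;
- experimental drugs: Day –28 or five half-lives, "whichever is longer, prior to Day 0 through Day 84".

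Instructions to Subjects uses the same end date for live vaccines and for tanning and UV sources. It closes by limiting the whole list of instructions to Day 84.

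**The concern.** Day 84 is the midpoint of treatment. From Day 85 a therapy on the list is still barred by the lead-in but is outside the window printed beside it. Study staff will meet this conflict, because concomitant medications are reviewed and recorded at weeks 16, 20 and 24.

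Take a patient who starts an immunosuppressant for a non-psoriasis condition at week 16. By the item's own dates the drug is not excluded and efalizumab continues. By the lead-in and the consequence sentence, efalizumab stops and the patient leaves the study.

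Three things are exposed:

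- **Safety.** Efalizumab suppresses T-cell function, and the protocol's list of serious events filed as safety reports includes Legionella pneumonia, vertebral osteomyelitis and abscesses. Whether a second immunosuppressant may overlap with it should not depend on which half of the section is read.
- **Consistency of discontinuation.** Two patients with the same co-medication could be handled differently.
- **Secondary data.** PASI is a secondary outcome through week 24, and biopsies after week 12 are triggered mainly by PASI relapse. Unbarred co-medication or uneven withdrawal affects both.

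The closing line of Instructions to Subjects adds to the problem. As written, it ends the reporting of new medications, infections and hypersensitivity while patients are still injecting at home.

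**Working it through.** The protocol states no figure to reproduce here. The check is a comparison of text plus day counts.

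**1. When does treatment end?** Day 84 / 7 = week 12, and 24 weeks × 7 = Day 168. No text defines the treatment period as ending at Day 84. Subject Discontinuation says that end-of-treatment procedures match those of the Day 84 visit. That borrows a list of procedures and does not move the end of treatment.

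**2. Does anything else in the visible text cover Days 85-168?**

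| Therapy | Dated item ends | Other bar after Day 84 | Result |
| --- | --- | --- | --- |
| Systemic psoriasis drugs | Day 84 | Largely covered: the list of permitted psoriasis medications applies in the screening and treatment periods, and rescue is allowed only after withdrawal ("If a subject experiences relapse of psoriasis after withdrawal from efalizumab, systemic or UV therapy may be used") | Conflicting wording |
| Live vaccines | Day 84 | Covered: the discontinuation criterion has no date or condition | Conflicting wording |
| Immunosuppressants, non-psoriasis indication | Day 84 | None: the discontinuation criterion covers only excluded treatment | Opposite handling |
| Experimental drugs | Day 84 | None: the same limitation applies | Opposite handling |

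For 2 of the 4 items the discontinuation criterion refers back to the list whose dates are in conflict, so it cannot settle the question.

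UV exposure, which is outside this list, follows the wording-only pattern. The inclusion criteria ask for avoidance for the duration of the study, while Instructions to Subjects dates the ban to Day 84.

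**3. Internal conflicts in Instructions to Subjects.** The live-vaccine item is tied to study drug being present, yet it ends at Day 84 while drug is still being given. The closing line ends every instruction at Day 84, although two items (blood donation, and the timing of inactivated vaccines) run to at least three months past the final injection.

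**4. How much of treatment is affected?**

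- Weekly dosing from Day 0 puts dose *k* on Day 7(*k* – 1), so dose 24 is on Day 7 × 23 = 161.
- Doses after Day 84 fall on Days 91, 98, …, 161: (161 – 91)/7 + 1 = 11, and 11/24 = 45.8%.
- If weeks 13-24 are counted as 12 self-injected doses, the share is 12/24 = 50%. Read as doses 13-24 (Days 84-161), one of the 12 falls on Day 84 itself. Read as Days 91-168 after clinic doses on Days 0-77, they leave a 14-day gap (Day 77 to Day 91) that does not fit weekly dosing. The figure of 11 is therefore preferred.
- Days 85-168 are 168 – 84 = 84 days, and 84/168 = 50%.
- PASI is scored at weeks 6, 12, 16, 20 and 24 within the week 6-24 secondary outcome, so 3 of 5 assessments fall after Day 84.

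**5. Would ending the bar at the last dose be enough?** No. It would end on Day 161, which is 168 – 161 = 7 days before the final PASI visit. It would also fall short of the study-long UV avoidance in the inclusion criteria.

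**The case against.** The strongest reply is that no sentence permits an immunosuppressant or experimental drug after Day 84. The lead-in, the Exclusion Criteria note and the consequence sentence all point to the stricter rule, and the word excluded in the discontinuation criteria can be read as referring to the lead-in. On that reading the Day 84 dates are leftover parentheticals and staff can simply follow the stricter text. The investigator may also stop treatment for any medical condition that threatens safety. Appendices G and H are not in the text available here, so a further bar there cannot be ruled out. Finally, the primary outcome is untouched, co-medication is recorded so affected patients could be identified, and the study is a single-arm mechanism trial of about 30 patients.

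Part of this stands. The stricter reading may well be what was intended, the statement that no other bar exists is limited to the visible text, and the consequence for data is confined to secondary and event-triggered assessments.

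It does not remove the conflict. Day 84 is not an isolated slip: it is attached to all four items and repeated as the operative limit for live vaccines, UV and the whole set of patient instructions. The investigator's discretion concerns medical conditions, not medications. Appendix G is described as a patient information sheet drawn from the drug label, and such a sheet would not rewrite the dates in Excluded Therapies.

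**Conclusion.** The concern holds. The section contradicts itself for Days 85-168, half of the treatment period, in which 11 of 24 doses are given. For immunosuppressants used for other indications and for experimental drugs, the two readings lead to opposite actions. For systemic psoriasis drugs, live vaccines and UV the fault is conflicting wording, because other text covers them wholly or largely.

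The counts assume weekly dosing from Day 0 without shifts. They measure exposure time, not harm: the document gives no rate of excluded-therapy use, so no effect on PASI is estimated. The Day 84 primary outcome and the scheduled biopsies at weeks 0, 2, 6 and 12 are unaffected. The point should be fixed because it concerns an operative safety and discontinuation rule and is cheap to correct. It does not threaten the main analysis.

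**What to change.** 1. In the four Excluded Therapies items, and in the live-vaccine and UV items of Instructions to Subjects, replace the Day 84 end date with: *through Day 168 (week 24) or the last dose of study drug, whichever is later; for a patient withdrawn early, through withdrawal from efalizumab.* The last clause keeps rescue therapy available after withdrawal. The whichever-is-later clause will rarely matter if dose 24 falls on Day 161, but it covers a late or visit-labelled final dose.
2. Replace the closing line of Instructions to Subjects with: *These instructions apply through the same date, and longer where an item says so.*
3. In Criteria for Discontinuation of Treatment, state that excluded treatment means treatment within that same window.

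The cost is date wording in these three sections and in the instruction sheet handed out on Day 0. Design, visits, sample size and analysis do not change.

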Eleven nonclinical studies have been performed to assess the safety, toxicology, pharmacokinetics, pharmacodynamics, and immunogenicity of efalizumab. Efalizumab was generally well tolerated in chimpanzees at doses of up to 40 mg/kg/wk administered for 26 weeks. Although the death of one chimpanzee was attributed to a chronic infection not associated with efalizumab treatment, a potential exacerbation of the infection by efalizumab cannot be ruled out. Administration of efalizumab at 38 mg/kg/wk resulted in a significant reduction in the humoral immune response; however, this effect appears to be reversible upon clearance of the drug.

Re-exposure to a single dose of efalizumab (up to 10 mg/kg) was well tolerated in chimpanzees. Only one chimpanzee in the toxicology studies developed an anti-efalizumab antibody response, but no adverse effects associated with this antibody response were noted in this animal. Cellular expression of CD11a was down‑regulated following efalizumab administration, and re‑expression occurred 7-10 days after efalizumab was eliminated from the blood.

The pharmacokinetics and pharmacodynamics of efalizumab in chimpanzees were similar to those seen in humans. Data from all species tested support that binding to CD11a plays an important role in the absorption, distribution, metabolism, and excretion of efalizumab. Together, these data were consistent with the understanding of the mechanism of action across species, and the doses selected were appropriate for understanding the effect of the proposed clinical doses.

For further information, see the Investigator Brochure.

Clinical Experience with Efalizumab

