This study will be conducted according to the International Conference on Harmonization E6 Guideline for Good Clinical Practice (GCP) and any federal, national, and local requirements.

Subject Discontinuation

Subjects may withdraw or be withdrawn from the study, at any time. Every effort will be made to obtain information on subjects who discontinue from the study prematurely. The procedures and assessments to be performed at the end of treatment visit will be the same as those for the Day 84 visit.

Criteria for Discontinuation of Treatment

The criteria for discontinuation of treatment include the following:

- Pregnancy
- Administration of a live virus or bacteria vaccine
- Initiation of excluded systemic treatment for psoriasis
- Initiation of excluded immunosuppressive treatment for any indication
- Initiation of excluded experimental medication or other treatment
- Any medical condition (e.g., opportunistic infections, malignancies, immune complex disorders) that the investigator determines may jeopardize the subject’s safety if he or she continues in the study.

Study Discontinuation

Genentech has the right to terminate this study at any time. Reasons for terminating the study may include the following:

- The incidence or severity of adverse events in this or other studies indicates a potential health hazard to subjects.

1. **Statistical Model**

Preliminary data suggest that patients responding to efalizumab have lower expression levels of cytokines associated with activation of T-cells (IL-12, -IFN, IL-8, iNOS, and STAT1) than patients not responding. The response had been determined by the expression of K16 mRNA and epidermal thickness on day 56.

To correlate overall response with overall cytokine expression, response and cytokine expression were scored using a novel application of u-statistics to multivariate data. In short, the (response or cytokine expression) profile of each patient (A) is compared one-by-one with the profiles of all other patients (Xi). If patient A has a higher observation for each of the (response or cytokine expression) variables than patient Xi, the score of patient A is increased by one, if all Xi variables are lower, the score is decreased by one. If some variables have higher observations, while others have lower observations, the score of patient remains unchanged.

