**Adverse Events (AEs)**

The Common Toxicity Criteria (CTC) Grading Scale v3.0 (<http://ctep.cancer.gov/forms/CTCAEv3.pdf>), a standard and widely used instrument, will be used to define, grade and attribute adverse events (AEs). Any AEs encountered during the study will be recorded, and AEs will be reported as outlined in the table below.

| **Type of AE** | **Report to:** | **Timeframe for reporting** | **Web Reference** |
| --- | --- | --- | --- |
| All AEs | RU IRB | Annually | <http://clinfo.rockefeller.edu/irb/irb-ind.htm>  Procedures Section 17 |
| Unexpected AEs > grade 2; Serious AEs | RU IRB | Within 2 working days* | <http://clinfo.rockefeller.edu/irb/irb-ind.htm>  Procedures Section 17 |
| Both serious and unexpected AEs | FDA, Sponsor | As soon as possible (phone, fax writing), but within 7 days* | <http://www.accessdata.fda.gov/scripts/cdrh/cfdocs/cfcfr/CFRSearch.cfm?fr=312.32> |

* time since discovery

All AEs will be reported directly to The Rockefeller University IRB and the ACCTS both orally at the annual meetings and in writing as an annual report in the protocol. The annual summary will include:

1-All AEs will be summarized in tabular form; including grade for all AEs, attribution information for grade 3 and 4, and dose reduction information where appropriate.

2-Total enrollment, demographics of enrollment, protocol violations current status of subjects (completed, ongoing, dropout), reasons for attrition, and number of subjects reaching primary endpoints.

3-Available research data, especially any that might provide evidence of early proof or dis-proof of the hypothesis.

Unexpected AEs (of grade 2 or greater severity) and any serious adverse event (SAE) will be reported to the **IRB** within 2 working days of discovery as directed by The Rockefeller University IRB Procedures Manual version date 2/3/07.

Unexpected AEs (of grade 2 or greater severity) and any serious adverse event (SAE) will be reported to the **FDA** and **Sponsor** as soon as possible after discovery by telephone, fax or writing, but within 7 days, and with a full written report within additional 8 calendar days. This conforms to standard good clinical practice (GCP) guidelines (ICH Tripartite Guideline. Clinical Safety Data Management: Definitions and Standards for Expedited Reporting, Part B, no 1)

Any IND Safety Reports received from the Sponsor will be filed with the IRB promptly.

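### The excluded-therapy rule takes the patient out of the study as well as off drug, so scheduled adverse-event collection ends at one undated end-of-treatment visit (minor)

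*Protocol*

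**What the plan says.** All places are in the protocol.

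- **Excluded Therapies.** Four classes are barred: systemic psoriasis treatment, immunosuppressants, live vaccines and experimental treatments. Every listed window closes at Day 84; the one for experimental treatments, for example, ends with the words "whichever is longer, prior to Day 0 through Day 84". For a patient who receives one of these during treatment, the rule is that "the subject should not receive any additional doses of study drug and should be discontinued from the study".
- **Criteria for Discontinuation of Treatment.** "The criteria for discontinuation of treatment include the following": the list then contains those same four classes, with pregnancy and medical conditions that endanger the patient. The heading concerns treatment, yet the last item asks about the patient's safety "if he or she continues in the study".
- **Subject Discontinuation.** "Every effort will be made to obtain information on subjects who discontinue from the study prematurely". Also: "The procedures and assessments to be performed at the end of treatment visit will be the same as those for the Day 84 visit". The Day 84 list includes a physical examination, a blood count with platelets and adverse-event recording. No day is set for the end-of-treatment visit.
- **Section 14, Adverse Events.** "Any AEs encountered during the study will be recorded".
- **Section 15, Procedures to Minimize Risks.** Safety rests on monitoring all adverse events after the first dose on Day 0, with no end date. Summaries are promised for infections and for events leading to withdrawal from treatment, among others.
- **Instructions to Subjects.** Patients are told to report signs of infection promptly. The instructions apply through Day 84.

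**The concern.** Stopping drug and leaving the study are different decisions, and the protocol does not keep them apart. The one explicit instruction for this situation joins them. If the site follows it as written, the patient has an end-of-treatment visit and then no planned contact at which adverse events are asked about.

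The patients concerned have had a live vaccine, a second immunosuppressant, another systemic psoriasis drug or an experimental drug on top of CD11a blockade. Later infections are of particular interest in them. The blockade also outlasts the last injection. The nonclinical section reports that in chimpanzees CD11a expression returned 7 to 10 "days after efalizumab was eliminated from the blood", and describes the pharmacodynamics as similar to those in humans. With no day fixed for the end-of-treatment visit, it may fall before recovery. The infection and withdrawal summaries promised in Section 15 would then be least complete in the co-exposed patients.

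**Working it through.** The protocol states no figure on this point, so the check is a comparison of rules followed by a count of visit days.

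**1. Do the two rules conflict?** Excluded Therapies says no more drug and out of the study. Criteria for Discontinuation of Treatment says treatment stops and is silent on study status. Silence does not contradict the first rule, so the text is ambiguous and the stricter instruction stands. The wording looks intended: Concomitant Therapy, just before it, says that changes in certain other medicines do not require leaving the study.

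**2. What is scheduled after removal?** One visit with Day 84 procedures. The effort to obtain information, the patient's own reporting of infections through Day 84 and the general monitoring statement in Section 15 all remain, but none sets a contact or a date.

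**3. Which visits are at issue?** Itemised visits that record adverse events: Days 0, 7, ..., 84 give 13, plus Days 112, 140 and 168, so 13 + 3 = 16.

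| Removed just after | Itemised visits remaining | Of these, clinic injection visits up to Day 77 | Remaining main time points | Days to Day 168 |
| --- | --- | --- | --- | --- |
| Day 0 | 15 | 11 | 15 − 11 = 4 | 168 − 0 = 168 |
| Day 28 | 11 | 7 | 11 − 7 = 4 | 168 − 28 = 140 |
| Day 77 | 4 | 0 | 4 − 0 = 4 | 168 − 77 = 91 |

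Staff give the injections in clinic for the first 12 weeks, so the visits up to Day 77 are also dosing visits and should not be counted as lost safety visits for a patient off drug. In every row the relevant remainder is Days 84, 112, 140 and 168. For removal at Day 84 itself it is three days, over 168 − 84 = 84 days.

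**4. What do completers get after their last dose?** There are 24 weekly doses from Day 0, so the last falls at 23 × 7 = Day 161. The last itemised visit is Day 168, which is 168 − 161 = 7 days later. That is one visit. The Abstract's every-other-week schedule for the second 12 weeks (weeks 14 to 24) also leaves only week 24, Day 168, after Day 161.

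**5. How many patients?** The protocol gives no rate of excluded-therapy use. As an assumption, take 0 to 3 of about 30. The upper end is the allowance in the Statistical Model for up to 10% non-completion from any cause (0.10 × 30 = 3), so it is a ceiling and not an estimate.

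**The case against.** The strongest reply is that a removed patient is no worse off than a completer after the last dose: each has one itemised visit. That stands. A reader might infer from the rule that removed patients get a shorter post-dose safety window, or that someone removed after Day 28 forgoes 11 safety visits. The documents support neither, as steps 3 and 4 show. The CD11a recovery time does not separate the groups either, since completers are last seen 7 days after their final dose. What does separate them is the co-exposure and the calendar time to Day 168.

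A second reply is that safety monitoring has no end date in Section 15, that patients are told to report infections, and that efforts will be made to obtain information on those who leave. This also stands in part. A reader might infer that adverse-event collection stops altogether; it does not. But none of these clauses schedules a contact for a removed patient, and none overrides the explicit instruction.

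Third, the study flowchart (Appendix H) and the patient information sheet (Appendix G) are not in the text available, so an arrangement there cannot be excluded. Elsewhere the protocol mentions blood analysis every two weeks after the last dose and a follow-up phase. Those concern mechanistic assays and are not extended to patients who have left the study.

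Fourth, this is an open-label mechanism study of about 30 patients on an approved drug, with no safety aim among its listed outcomes, and the number affected may be zero. That limits the weight of the point and is why it is graded minor.

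**Conclusion.** The point holds in a limited form. The literal rule ends scheduled adverse-event collection at one visit of unspecified timing for patients who receive an excluded therapy by Day 84. The loss is scheduled calendar follow-up to Day 168, between 84 days (removed at Day 84) and just under 168 days (removed just after Day 0), covering at most four main time points per patient.

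It rests on three assumptions: that the site follows the Excluded Therapies wording literally, that the appendices not shown add no follow-up, and that very few patients are affected (0 to 3 of about 30, assumed).

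A reader might go further and call the two sections contradictory, or expect bias in the primary analysis. The documents do not support either. The sections are ambiguous on study status, and the end-of-treatment visit carries the Day 84 procedures, biopsy included. No endpoint, sample size or planned inference turns on this. A statistical analysis plan could not supply events that were never collected, so the protocol is the place for the change. Severity: minor; a cheap improvement.

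**What to change.** In Excluded Therapies, end the sentence once it has said that no further doses are given, and drop the clause on leaving the study. Then add text to this effect: *The patient has the end-of-treatment visit described under Subject Discontinuation. Unless he or she withdraws, the patient then remains in the study for recording of adverse events and concomitant medication, by telephone or visit, at those of Days 84, 112, 140 and 168 still to come. No further biopsies are taken.*

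These are days on which the trial already runs visits. The cost is one wording change and up to about four short contacts per affected patient. Under the assumed 0 to 3 patients that is 0 to 3 × 4 = 12 contacts in all. The downside is a little staff time, and that a patient who has stopped drug is asked to stay in touch until Day 168.
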